## Objectives

2

The objectives of this study are:

To assess the feasibility of implementing the mixed herb aromatherapy intervention in a clinical setting. Key metrics include recruitment rates, adherence rates, completion rates and safety assessment.To gather preliminary data on the efficacy of mixed herb aromatherapy on PSD, including symptom relief and improvements in the quality of life of the patients.To compare the preliminary effects of aromatherapy versus routine treatment and CBT for PSD patients, focusing on differences in symptom recovery and sustainability of treatment effects.To explore the impact of aromatherapy on brain function assessments (EEG and fNIRS) and its correlation with the recovery of patients suffering from PSD. This study will utilize EEG and fNIRS to assess the impact of aromatherapy on brain function in PSD patients and investigate the correlation between these brain function changes and the recovery progress of the patients.

## Trial design

3

A single-blind, pilot randomized controlled trial will be conducted to evaluate the preliminary efficacy and feasibility of mixed herb aromatherapy compared to standard care and CBT. This study will enroll ninety-nine post-stroke patients with PSD at the Second Rehabilitation Hospital of Shanghai. Prior to initiating rehabilitation, demographic details of all participants, including name, gender, age, education level, and medical history, will be collected. A centralized, web-based service provided by Research Randomizer (https://www.randomizer.org/) will be utilized to generate a randomization sequence, ensuring an even distribution of patients between the three groups: the non-active control group (receiving standard care), the aromatherapy group (undergoing daily aromatherapy inhalation), and the CBT group (receiving CBT sessions twice weekly) in a 1:1:1 ratio. The intervention will last for four weeks.

Primary feasibility outcomes will include recruitment rates, adherence to the intervention and completion rates. Recruitment rates will be monitored and documented weekly. Adherence will be tracked through participant logs, ensuring that each session is recorded. Completion rates will be calculated at the study’s conclusion.

Evaluation of intervention effectiveness will be conducted at three time points: before the intervention (baseline), immediately after the intervention (four weeks), and one month post-intervention, to assess the effectiveness of the treatments (see **Figure 1** for details).

**Figure 1 f1:**
[figure not shown]
Clinical Trial Flow Chart.

## Methods: participants, interventions and outcomes

4

### Study setting

4.1

This study will be conducted at the Second Rehabilitation Hospital of Shanghai, China. This hospital is a comprehensive rehabilitation institution offering multidisciplinary rehabilitation treatment services, equipped with the facilities and professional staff required for the execution of this study. Located in the central area of Shanghai, the hospital is easily accessible for participants. Data will be collected in China.

#### Eligibility criteria

4.1.1

##### Inclusion criteria

4.1.1.1

- Diagnosed by cranial CT or MRI and meeting the diagnostic criteria for stroke as revised by the 4th Cerebrovascular Disease Conference.

- Meet the diagnostic criteria for depression in Chinese Classification and Diagnostic Criteria for Mental Disorders CCMD-3.

- Age 30~80 years old, gender is not limited.

- PHQ-9 score ≥5.

- No severe cognitive impairment.

- Those with no history of depression before stroke.

- Normal sense of smell.

- Informed consent and voluntary enrollment in the study.

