#### Who will take informed consent?

4.1.2

In this clinical trial, the responsibility for ensuring that potential participants understand and agree to participate will be assumed by qualified and professionally trained members of the research team, which primarily includes the Principal Investigator in charge of the project and/or the Clinical Research Coordinator. These professionals have completed comprehensive training in ethical research practices, including Good Clinical Practice (GCP) certification, to ensure that they have the ability to communicate with potential participants in a clear, detailed and non-coercive manner. The informed consent process will be conducted through a series of detailed and transparent steps to ensure that each potential participant fully understands the objectives, process, possible risks and benefits of the study, as well as their rights and obligations. This process includes providing a comprehensive Participant Information Sheet (PIS) that details the study’s purpose, procedures, potential risks and benefits, confidentiality and data security measures, and the voluntary nature of participation, including contact information for the research team. Eligible patients will be given at least 48 hours to review the PIS, ask any questions, and discuss their potential participation with family, friends, or healthcare providers if they wish. This period is designed to ensure that patients do not feel rushed and can thoroughly consider all aspects of the study before providing their consent. This process involves a one-on-one meeting with the participant, during which the researcher will brief them in detail about the study and answer any questions, ensuring that each participant fully understands the study’s objectives, procedures, possible risks and benefits, and their rights and obligations. Written consent will only be collected when it is confirmed that the participant has been fully informed of all relevant information and is voluntarily agreeing to take part in the study. Patients included in this study will not have severe cognitive impairment, but for those participants with limited mobility, consent will be sought from their legal guardian or authorized agent, ensuring that the agent fully understands the research and consents on behalf of the participant. By implementing these measures, we are committed to upholding the rights of participants and ensuring that the research complies with ethical and legal standards.

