#### Primary outcome measures

4.3.1

1. Recruitment rates: Recruitment rates will be calculated as the proportion of successfully recruited eligible participants within the specified period, documented weekly, and reported as a percentage of the total planned recruitment. A recruitment rate of at least 70% will be considered acceptable.

2. Intervention adherence: Intervention adherence will measure the proportion of participants who complete the intervention as planned. This will be tracked using participant logs that record the completion of each aromatherapy session, CBT session, and conventional treatment session. Adherence to each component will be reported weekly. An adherence rate of at least 80% will be considered acceptable. Additionally, feasibility outcomes will include the proportion of participants who complete all assessments as scheduled, assessing the practicality of integrating aromatherapy with existing treatments.

3. Assessment completion: Assessment completion will assess the proportion of participants who complete all scheduled assessments and follow-ups. This will be calculated and reported at the end of the intervention. A completion rate of at least 85% will be considered acceptable.

5. Safety Assessment: Safety will be evaluated through subjective and objective measures. Participants will report any discomfort or adverse reactions, and vital signs (heart rate, respiratory rate, blood pressure) will be monitored before and after each session. An adverse event log will document all incidents and management actions. Adverse reactions will be categorized as mild, moderate, or severe.

- Moderate: Noticeable symptoms that may interfere with daily activities but are not life-threatening, requiring medical intervention or short-term observation.

- Severe: Symptoms significantly impacting daily life, potentially life-threatening, requiring intensive medical intervention such as hospitalization or emergency medication.

An acceptable safety threshold is set at no more than 10% of participants experiencing moderate to severe adverse reactions.

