### Sample size and feasibility criteria

4.5

Since this study employs a novel mixed herbal aromatherapy intervention, there is no prior research directly comparable to reference. As this is a pilot RCT, the focus is on assessing the feasibility of the intervention rather than hypothesis testing. Therefore, the sample size estimation is not based on power analysis but according to rule of thumb.

Based on the guidance from Billingham et al. (49), a sample size of approximately 30 participants per group is considered appropriate for a pilot study. This sample size is justified by the need to gather preliminary data on feasibility outcomes, such as recruitment rates, adherence rates, and completion rates, and to ensure sufficient variability and precision in the estimates.

Taking into account 10% potential dropout rates, we will aim to recruit approximately 33 participants per group to ensure we have enough data for the feasibility analysis. This will result in a total sample size of approximately 99 participants across the three groups.

The predefined criteria for feasibility outcomes are:

- Recruitment rate of at least 70%: This is considered a reasonable and achievable target for pilot studies to ensure adequate participant recruitment.

- Adherence rate of at least 80%: This reflects a high level of participant engagement and compliance with the intervention protocol, which is crucial for obtaining reliable data.

- Completion rate of at least 85%: This indicates that the majority of participants complete the study, ensuring data integrity and minimizing the impact of dropouts on the study results.

These criteria will help determine the feasibility of conducting a full-scale RCT.

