#### Primary outcome analysis: feasibility metrics

8.1.1

Recruitment, adherence, and completion rates will be the focus, analyzed descriptively to provide insights into the practical implementation and scalability of the intervention. Each metric will be reported as a percentage:

- Recruitment rate: Proportion of eligible participants who were successfully recruited.

- Intervention adherence: Proportion of participants who adhered to the intervention throughout the study.

- Assessment completion: Proportion of participants who completed all assessments and follow-ups.

- Safety assessment: Safety will be evaluated through subjective and objective measures, including monitoring vital signs and documenting adverse reactions.

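### The denominator of the primary recruitment rate is not fixed: planned recruitment in 4.3.1, eligible participants in 8.1.1, and 'eligible' itself can include or exclude patients who refuse

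*Protocol article*

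**What the plan says.** Recruitment is a primary feasibility outcome, and the protocol article describes it in three places.

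- **Section 4.3.1 (Primary outcome measures):** "Recruitment rates will be calculated as the proportion of successfully recruited eligible participants within the specified period", and this is then "reported as a percentage of the total planned recruitment". The same item sets the mark: "A recruitment rate of at least 70% will be considered acceptable".
- **Section 4.5 (Sample size and feasibility criteria):** the mark is repeated without a denominator: "Recruitment rate of at least 70%: This is considered a reasonable and achievable target for pilot studies". This section also gives the planned total of about 99 and says the criteria will help to judge whether a full-scale trial is feasible.
- **Section 8.1.1 (Primary outcome analysis: feasibility metrics):** "Recruitment rate: Proportion of eligible participants who were successfully recruited".

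Two senses of 'eligible' appear elsewhere.

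- **Section 4.1.1.1 (Inclusion criteria):** the last of the eight criteria is "Informed consent and voluntary enrollment in the study".
- **Section 4.1.2 (Who will take informed consent?):** "Eligible patients will be given at least 48 hours to review the PIS". Patients are called eligible here before they have agreed to anything.
- **Section 5.3 (Implementation):** this reads the same way as 4.1.2. Staff screen for eligibility, and allocation follows consent.

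**The concern.** A rate with a pass mark needs one denominator. Here there are two stated denominators, and one of them splits again according to whether agreeing to take part belongs to eligibility. That leaves three candidate rates for one primary outcome:

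- **A:** recruited, divided by eligible patients, with consent counted as an eligibility criterion (4.1.1.1 read with 8.1.1);
- **B:** recruited, divided by patients who meet every criterion other than consent (4.1.2 and 5.3 read with 8.1.1);
- **C:** recruited, divided by the planned 99 (4.3.1).

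They answer different questions. B measures willingness to accept randomisation and, for a third of patients, daily inhalation of smoke from lit herbs. C measures whether the hospital can supply enough patients in the period. A measures little more than losses between consent and enrolment. If the choice is left open, the denominator could be chosen after the counts are known, and a reader of the results could not tell whether a pass means that patients were willing to join.

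**Working it through.** **Inputs from the protocol article.** About 30 per group, a 10% dropout allowance, three groups and about 99 in total (4.5); the 70% mark (4.3.1 and 4.5). The article gives no figure for clinically eligible patients, consent or refusals, so those below are assumptions shown over a range.

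**The planned total.** 30 × 1.10 = 33 per group; 33 × 3 = 99. The stated figure is reproduced and serves as the denominator of C.

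**Pass marks by reading**

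- **C:** 0.70 × 99 = 69.3, so 70 recruited passes (70/99 = 70.7%) and 69 fails (69/99 = 69.7%).
- **B, with 99 recruited:** 99/0.70 = 141.4. With 42 refusals the rate is 99/141 = 70.2% (pass); with 43 it is 99/142 = 69.7% (fail).
- **A, with 99 recruited:** 99/99 = 100% for any number of refusals. This assumes that nobody is lost after consenting and that recruitment stops at 99. Failure needs more than 30% of consenters to be lost before enrolment. With 99 consenters and an assumed 10% loss, the exact binomial chance of enrolling at least 70 is above 0.9999.

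**The same data under the three readings (30% consent assumed)**

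| Clinically eligible | Recruited | A | B | C |
|---|---|---|---|---|
| 100 | 100 × 0.30 = 30 | 30/30 = 100% | 30/100 = 30.0% | 30/99 = 30.3% |
| 200 | 200 × 0.30 = 60 | 60/60 = 100% | 60/200 = 30.0% | 60/99 = 60.6% |
| 300 | 300 × 0.30 = 90 | 90/90 = 100% | 90/300 = 30.0% | 90/99 = 90.9% |

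Consent is equally poor in every row. A always passes and B always fails. C fails in the first two rows and passes in the third, because the pool is larger.

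The disagreement also runs the other way. If only 69 clinically eligible patients exist and all of them consent, B is 69/69 = 100% (pass) and C is 69/99 = 69.7% (fail).

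**Does B discriminate?** Take 142 clinically eligible patients. A pass needs 0.70 × 142 = 99.4, so 100 recruited, setting aside the cap at 99. The exact binomial chance of passing is below 0.0001 at a true consent rate of 50%, 0.006 at 60%, 0.50 at 70% and 0.998 at 80%. On this reading the mark responds to willingness to join.

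**The case against.** A reader might infer something stronger: that because consent is an inclusion criterion, refusers always drop out of the denominator and the 70% criterion is almost impossible to fail. The documents do not support that.

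- Section 4.3.1 sets the 70% directly after naming planned recruitment as the base. On that base, who counts as eligible does not change the denominator, and 69 or fewer recruited is a failure.
- Sections 4.1.2 and 5.3 point to the pre-consent sense of 'eligible', in which refusers stay in. Reading A is literally available but is probably not what the sponsor means.
- A consent line among the inclusion criteria is routine. It says that nobody enters without agreeing, and is not in itself an error.
- Section 4.5 says only that the criteria help to judge feasibility, so missing the 70% mark need not by itself reverse the decision.
- The flow chart (Figure 1) is not shown and the article is condensed. It cannot be said that refusals go unrecorded.

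All of this stands, and it limits the point to an inconsistent definition. It does not remove it. Sections 4.3.1 and 8.1.1 both state a definition and the two differ, so this is a conflict within the text and not detail left to a fuller document. Reading C does not rescue the measure either, since 90/99 = 90.9% passes with 70% of clinically eligible patients refusing.

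**Conclusion.** The point holds as an inconsistency in a primary outcome: two stated denominators, one of which has two readings. The documents do not establish which is intended.

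Its effect can be large. With an assumed 300 clinically eligible patients and 30% consent, the result is about 100%, 90.9% or 30%, hence two passes and one fail. With the full 99 recruited, the clinically eligible rate crosses the mark between 42 and 43 refusals, while the other two readings stay at 100%. Only the planned-recruitment and clinically eligible readings can realistically fail, and only the clinically eligible one measures willingness to join.

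The pool sizes and consent rates are illustrative assumptions; the conflict between the definitions does not depend on them. Severity is minor to moderate: the wording is easily repaired, but it governs a criterion that feeds the decision on a full-scale trial.

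**What to change.** Use one definition in 4.3.1, 4.5 and 8.1.1. The recruitment rate is randomised patients divided by screened patients who meet every criterion in 4.1.1.1 other than consent and none in 4.1.1.2, with refusals kept in the denominator. Apply the 70% mark to that rate. Report recruitment against the target of 99 within the period as a separate measure, under its own name. The consent line can stay in 4.1.1.1 as a condition of enrolment, provided the outcome definition says that it does not count towards the denominator.

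The cost is wording in three sections and a record of refusals, preferably with reasons. The article describes no screening log. Section 4.6 has the recruiters documenting medical histories and 4.3.1 has weekly recruitment records, so recording refusals may be a small new task. The reported rate may also look less favourable than it would on either of the other readings.

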##### Exclusion criteria

4.1.1.2

- Stroke patients with unstable condition.

- Patients with serious bone, joint, and muscle disorders; liver or kidney diseases; other serious life-threatening diseases (e.g., advanced cancer, severe cardiovascular diseases, severe respiratory diseases, end-stage liver or kidney diseases); and serious mental illnesses such as schizophrenia or severe bipolar disorder.

- Patients with severe speech, visual and hearing impairments.

- Patients who have received aromatherapy within one month.

- Patients with asthma, history of respiratory diseases such as allergy to flowers, plants and essential oils.

- Patients with scalp trauma, skin breakdown, redness, inflammation, or soft tissue damage that would interfere with the examination.

- Patients with a history of seizures.

- Patients undergoing other clinical trials.

##### Withdrawal or dropout criteria

4.1.1.3

- Participants with incomplete or false information.

- Participants with adverse events.

- Participants who are not suitable for continuing treatment due to other systemic diseases for various reasons.

- Participants who voluntarily proposed to withdraw from the study.

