### Plans to promote participant retention and complete follow-up

7.2

The follow-up of this study is scheduled 4 weeks after the end of the intervention. Regular contact will be maintained with participants by phone, email, or text message to provide study progress updates, answer participant questions, and remind of upcoming follow-up visits.

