### Methods in analysis to handle protocol non-adherence and any statistical methods to handle missing data

8.4

Missing data and any data collected that is not in compliance with the protocol will be removed from the data analysis.

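### Incomplete or false information is an unrestricted withdrawal criterion, so a randomised participant can leave the study over a missing record while later outcomes are still obtainable

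*Protocol article*

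**What the plan says.** Section 4.1.1.3 of the protocol article, on withdrawal or dropout, has four entries. The first is "Participants with incomplete or false information". The entry does not say which information is meant, how much must be missing, at which visit, or whether meeting it ends treatment, follow-up or inclusion in the analysis.

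Other sections bear on it:

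- Section 3 sets three assessment points: "before the intervention (baseline), immediately after the intervention (four weeks), and one month post-intervention".
- Section 4.3.1 makes completeness a primary feasibility outcome: "Assessment completion will assess the proportion of participants who complete all scheduled assessments and follow-ups". Its criterion is "A completion rate of at least 85% will be considered acceptable".
- Section 4.2.3 deals separately with discontinuing or modifying the allocated intervention.
- Section 7.2 promises retention efforts: "Regular contact will be maintained with participants by phone, email, or text message". It does not mention participants who have been withdrawn.
- Section 8.4 handles missing values at the analysis stage: "Missing data and any data collected that is not in compliance with the protocol will be removed from the data analysis".

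No section says that withdrawn participants continue to be assessed, and none says that they do not.

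**The concern.** Missing information is something this pilot sets out to measure, and section 4.1.1.3 also makes it a ground for exit. Leaving the study is a natural reading. Stopping treatment has its own section (4.2.3), and the last entry in the same list, on voluntary withdrawal, refers to the study and not to the treatment.

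Two things are at stake.

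- **Lost outcomes.** A participant with a gap at baseline or week 4 may never have the one-month scales taken, although that visit is already planned. This differs from the deletion rule in section 8.4. Deletion acts on data in hand and can be reversed in a later analysis, but data never collected cannot be recovered.
- **Selection.** The third objective compares the arms on the sustainability of treatment effects, which rests on the one-month sample. Participants with gaps in their records may well differ from the rest, so removing them after randomisation leaves a selected group.

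False information discovered after randomisation has the same effect: it becomes a post-randomisation exclusion.

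**Working it through.** **1. The sample size that the rule acts on.** Section 4.5 says that "a sample size of approximately 30 participants per group is considered appropriate for a pilot study", allows 10% dropout, and arrives at about 33 per group and 99 in total.

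- 30 × 1.10 = 33, and 30 / 0.90 = 33.3, which rounds up to 34. Both agree with about 33.
- 3 × 33 = 99.
- 33 × 0.90 = 29.7, so the allowance leaves about 30 per arm.

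The plan's figures are reproduced and are not in dispute.

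**2. Follow-up lost under the strict reading.** The documents give no rate of missed or partial visits, so it is assumed. Let m be the probability that something is missing at a given post-baseline visit, the same at week 4 and at one month, and independent between the two. The strict reading is that a gap at week 4 ends participation.

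- Complete one-month assessments if participants are kept: 99(1 − m)
- Complete one-month assessments under the strict reading: 99(1 − m)²
- Loss due to the rule: the difference, 99m(1 − m)

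| m | Kept | Strict reading | Lost | Lost per arm |
|---|---|---|---|---|
| 2% | 97.02 | 95.08 | 1.94 | 0.65 |
| 5% | 94.05 | 89.35 | 4.70 | 1.57 |
| 10% | 89.10 | 80.19 | 8.91 | 2.97 |
| 15% | 84.15 | 71.53 | 12.62 | 4.21 |

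At m = 10%, keeping participants leaves 89.10 / 3 = 29.7 per arm at one month, the same number that the plan's dropout allowance gives. The strict reading leaves 80.19 / 3 = 26.7.

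The loss shrinks if gaps cluster in the same people, because someone who misses week 4 and would have missed one month anyway costs nothing extra. The table leaves out exits triggered by baseline gaps, session logs or false information.

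**3. Effect on the assessment-completion outcome.** Under the section 4.3.1 definition, a participant completes only if every scheduled assessment is done. For the two post-baseline visits that probability is (1 − m)² whether or not the participant is withdrawn after a week-4 gap: 96.04%, 90.25%, 81.00% and 72.25% at the four values of m. The rule therefore does not move this percentage when the missing item is a scheduled assessment. It could do so only when the trigger is something else, such as a medical-history item or a session log, in a participant who would otherwise have completed every assessment.

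**The case against.** The strongest objection is that the entry may not concern outcome assessments at all. It is paired with false information and sits under the eligibility heading (4.1.1). Section 7.4 describes the personal information collected as demographic details and medical history. A skipped questionnaire is not naturally called false. Sections 4.3.1 and 8.4 also treat missing values as something to count or to drop from analysis, without mentioning study exit. This stands as far as it goes: the text is ambiguous. But the narrow reading still lets a randomised participant be removed over paperwork that should be settled before randomisation.

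A second objection is that a condensed article may leave operational definitions to the full protocol. That would answer a complaint about missing detail. Here a rule is stated, and stated without limits, so a site could follow it as written.

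Three stronger inferences are tempting, and the documents do not support them.

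- **A reader might infer that one missed assessment automatically removes a participant and ends data collection.** No section says so. It is one permitted reading.
- **A reader might infer that the rule threatens the 85% completion criterion.** Anyone with a missed assessment already fails that definition, withdrawn or not.
- **A reader might infer that unblinded treating staff would apply it unevenly between arms.** The protocol does not say who applies it. Sections 5.1, 5.2 and 6.1 have outcomes collected by blinded researchers, and section 5.3 keeps the person administering the intervention out of outcome assessment.

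**Conclusion.** The point holds in a limited form. Section 4.1.1.3 states a withdrawal criterion that is neither confined to pre-randomisation eligibility data nor explicit about whether it ends treatment or study participation. On the broad or the narrow reading it allows randomised participants to be removed for administrative reasons, so that one-month outcomes that could still be obtained may not be collected and the sample for the third objective becomes selected.

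The size cannot be computed from the documents. The figure of about 2 to 13 of 99 one-month assessments rests on assumed per-visit miss rates of 2% to 15%, independence between visits, and the strict reading. With clustering of gaps within participants, or with the narrow reading, it would be smaller. The correction is worth making because the loss would be irrecoverable and the visits are already scheduled.

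**What to change.** 1. In section 4.1.1.3, restrict the entry to eligibility information that is checked before randomisation, and remove it as a ground for withdrawal after randomisation.
2. State that a participant with a missed or partial assessment stays in the study in the allocated arm, is scored as not complete for assessment completion, and is invited to every later assessment.
3. State that false or missing eligibility information found after randomisation is logged as a protocol deviation, with follow-up continued.
4. Carry the same wording into sections 7.2 and 8.4, so that retention and missing-data handling agree with it.

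The cost is a few lines of protocol text, with no new visits or procedures. The downside is that some participants will contribute partial records. Keeping the check on eligibility information before randomisation preserves whatever safeguard the entry was meant to provide.

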#### Criteria for discontinuing or modifying allocated interventions

4.2.3

For patients with PSD who received the aromatherapy inhalation intervention, if a serious adverse reaction (e.g., an allergic reaction) occurs during the treatment, the research team will immediately stop the treatment for that participant and carry out the necessary medical interventions. At the same time, if the participant voluntarily requests to stop the treatment, we will record his/her request and respect his/her decision. Participants’ depressive symptoms will be regularly assessed in the study and adjustments to the treatment regimen will be considered if significant improvement or worsening is observed. All these adjustments will be made under the guidance of the research ethics committee to ensure that the safety and rights of the participants are protected.

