### Adverse event reporting and harms

9.3

The study is not expected to result in serious adverse reactions and the risk assessment will be monitored by clinicians. In the event of an adverse reaction caused by aromatic sniffing, we will promptly treat or withdraw the participant from the study. In the meantime, we will record the details in the case report form.

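### Section 4.1.1.3 makes any adverse event a withdrawal or dropout criterion, which does not fit sections 4.2.3, 9.3 and 4.3.1 and, if applied as written, feeds into the primary completion rate

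*Protocol article*

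**What the plan says.** Four places in the protocol article bear on what happens after an adverse event.

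- **Section 4.1.1.3 (Withdrawal or dropout criteria)** has four bullets. One reads, in full, "Participants with adverse events". It names no grade, no causal link to treatment and no arm.
- **Section 4.2.3 (Criteria for discontinuing or modifying allocated interventions)** covers participants receiving aromatherapy: "if a serious adverse reaction (e.g., an allergic reaction) occurs during the treatment, the research team will immediately stop the treatment for that participant". It does not mention leaving the study.
- **Section 9.3 (Adverse event reporting and harms)** says: "In the event of an adverse reaction caused by aromatic sniffing, we will promptly treat or withdraw the participant from the study".
- **Section 4.3.1 (Primary outcome measures)** says: "Adverse reactions will be categorized as mild, moderate, or severe". Its limit covers only the upper grades: "An acceptable safety threshold is set at no more than 10% of participants experiencing moderate to severe adverse reactions".

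Section 4.3.1 also defines the outcome that withdrawal affects: "Assessment completion will assess the proportion of participants who complete all scheduled assessments and follow-ups". At least 85% is acceptable. Section 4.5 says of the recruitment, adherence and completion thresholds: "These criteria will help determine the feasibility of conducting a full-scale RCT". On attrition it says: "Taking into account 10% potential dropout rates, we will aim to recruit approximately 33 participants per group". It does not say which causes of dropout the 10% covers.

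Section 7.2 describes general contact and reminders. Section 8.4 removes missing data from the analysis.

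**The concern.** The same event leads to different actions depending on which section is followed. A brief, mild headache in the aromatherapy arm meets a withdrawal criterion in 4.1.1.3, calls for no action in 4.2.3, may simply be treated under 9.3, and lies outside the safety limit in 4.3.1. An unrelated event in the CBT or control arm meets a criterion in 4.1.1.3 and is not addressed in 4.2.3 or 9.3.

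Two things are at stake if the bullet is followed as written.

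- **The completion rate.** It is a primary feasibility outcome with a pass mark. It would partly measure the protocol's own withdrawal rule instead of participants' willingness and ability to stay, and it would count mild events that the safety criterion accepts.
- **The clinical data.** Week-4 and one-month values would be missing selectively in participants who had an event. This includes values used for the aromatherapy-versus-CBT non-inferiority comparison in section 8.1.2. If event rates differ between arms, so does the loss.

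**Working it through.** **Side-by-side reading**

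| Section | Trigger | Arm | Consequence |
|---|---|---|---|
| 4.1.1.3 | any adverse event | not limited | withdrawal or dropout criterion |
| 4.2.3 | serious adverse reaction | aromatherapy | treatment stopped |
| 9.3 | reaction caused by the aroma | aromatherapy | treated, or withdrawn from the study |
| 4.3.1 | moderate or severe reaction | not limited | counts towards the 10% limit |

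Sections 4.1.1.3 and 4.2.3 differ in both trigger and consequence. Section 9.3 overlaps with 4.1.1.3, because withdrawal is one of its options, but it is narrower in trigger and arm.

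**The plan's own figure.** Section 4.5 starts from 30 per group and adds 10%: 30 × 1.10 = 33, and 3 × 33 = 99. Dividing instead gives 30 / 0.90 = 33.3, close enough for an approximate figure. The sample size is not in question.

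**Counts implied by the protocol's thresholds**, taking all 99 randomised participants as the denominator:

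- Completion: 85/99 = 85.9% passes and 84/99 = 84.8% fails. At most 99 − 85 = 14 may be non-completers.
- Safety: 9/99 = 9.1% passes and 10/99 = 10.1% fails. Nine moderate-to-severe reactions are tolerated.
- If those nine are all withdrawn, 14 − 9 = 5 losses (5/99 = 5.1%) remain for mild events and every other reason.
- Fifteen mild events alone (15/99 = 15.2%), each leading to withdrawal, would miss the completion criterion with no moderate-to-severe reaction at all.

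**Chance of at least 85 completers.** The protocol gives no event rate, so everything after the first line below is illustrative. Those lines assume that every event leads to withdrawal and that event withdrawals come on top of 10% other dropout. Unless stated otherwise, events and other dropout are taken as independent. Write e for the event rate.

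- The 10% already includes event withdrawals: P(Binomial(99, 0.90) ≥ 85) = 0.93. No effect against plan.
- Events in the aromatherapy arm only, with completers distributed as Binomial(33, 0.90 × (1 − e)) + Binomial(66, 0.90):
  - e = 5%: expected completion 88.5%, probability 0.84
  - e = 10%: expected completion 87.0%, probability 0.70
  - e = 20%: expected completion 84.0%, probability 0.36
- Events at 10% in all arms: completion 0.90 × 0.90 = 0.81, probability 0.13. If events and other dropout never overlap, completion is 0.80 and the probability 0.09.

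**Break-even event rate**, where expected completion equals 85% under the same assumptions:

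- All arms: 1 − 0.85/0.90 = 5.6%.
- Aromatherapy arm only: 3 × 5.56% = 16.7%.

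**The case against.** The strongest reply is that 4.1.1.3 is a list of categories and contains no instruction. Its last bullet, voluntary withdrawal, is a reason for leaving and not a trigger that the team applies. On that reading an adverse event is only a possible ground for withdrawal, and 4.2.3 and 9.3 govern what is done. The sections also partly answer different questions: leaving the study, stopping the intervention, and managing a reaction. This is a fair reading, but the text does not state it. The bullet on other systemic diseases is limited to participants unsuited to continuing treatment, and the adverse-event bullet has no such limit. Staff who follow the list as written would withdraw people whom the other sections would keep.

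Other parts of the reply stand.

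- The mismatch with 9.3 is partial, since 9.3 itself allows withdrawal. A reader might infer a flat contradiction there, and the text does not support one.
- A reader might treat the lack of any statement on continued assessment as a defect in itself. A journal article may leave that to the full protocol. It matters here only because the stated rule points towards withdrawal.
- A reader might infer that safety data are lost. They are not: 4.3.1 requires an adverse event log and 9.3 requires details in the case report form, so the safety proportion can still be computed.
- The natural place for event withdrawals is inside the 10% dropout allowance, because 4.1.1.3 classes them with dropout and 4.5 excludes no cause.
- Completion informs the feasibility decision without fixing it, and the logs would let the team trace a shortfall to events. Removal of missing data under 8.4 applies whatever the cause and is a separate matter.

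**Conclusion.** The point holds as an unqualified withdrawal criterion that is inconsistent with 4.2.3, broader than 9.3, and at odds with the tolerance of mild reactions in 4.3.1. It is a stated rule that does harm if followed, so it is more than missing detail. It should be corrected because it touches a primary feasibility criterion and the selective availability of the week-4 and one-month data.

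Its size is unknown. The firm figures are the counts: at most 14 of 99 may be lost, and 9 moderate-to-severe reactions are tolerated. Both take all 99 randomised as the denominator. It is tempting to conclude that the trial will probably miss its completion criterion. The documents do not support that. Every probability below 0.93 needs a mandatory reading of the bullet, an assumed event rate, and event withdrawals added to the 10% dropout, and the protocol states none of these. Whether the loss is unequal between arms likewise depends on event rates that the protocol does not give.

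**What to change.** Replace the adverse-event bullet in 4.1.1.3 with one investigator-judged rule for stopping the allocated intervention, and word 4.2.3 and 9.3 to match it. For example: *An adverse event leads to stopping the allocated intervention only if the investigator judges that continuing is unsafe. Stopping the intervention is not withdrawal from the study. Unless consent is withdrawn, the participant completes the week-4 and one-month assessments and stays in the safety, completion and clinical analyses as randomised.*

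The cost is wording in three sections and a small added effort to follow participants who would otherwise have been withdrawn. The visits are already scheduled for everyone and the sample size does not change. Participants can still stop treatment for safety or withdraw consent. At the planned 10% dropout, expected completion stays at 90%, with a 0.93 chance of at least 85 completers.
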